## Abstract

**Background:**

Anorexia nervosa is a serious eating disorder leading to high morbidity and mortality as a result of both malnutrition and suicide. The seriousness of the disorder requires extensive knowledge of effective treatment options. However, evidence for treatment efficacy in this area is remarkably weak. A recent Cochrane review states that there is an urgent need for large, well-designed treatment studies for patients with anorexia nervosa. The aim of this particular multi-centre study is to evaluate the efficacy of two standardized outpatient treatments for patients with anorexia nervosa: focal psychodynamic (FPT) and cognitive behavioural therapy (CBT). Each therapeutic approach is compared to a "treatment-as-usual" control group.

**Methods/Design:**

237 patients meeting eligibility criteria are randomly and evenly assigned to the three groups – two intervention groups (CBT and FPT) and one control group. The treatment period for each intervention group is 10 months, consisting of 40 sessions respectively. Body weight, eating disorder related symptoms, and variables of therapeutic alliance are measured during the course of treatment. Psychotherapy sessions are audiotaped for adherence monitoring. The treatment in the control group, both the dosage and type of therapy, is not regulated in the study protocol, but rather reflects the current practice of established outpatient care. The primary outcome measure is the body mass index (BMI) at the end of the treatment (10 months after randomization).

**Discussion:**

The study design surmounts the disadvantages of previous studies in that it provides a randomized controlled design, a large sample size, adequate inclusion criteria, an adequate treatment protocol, and a clear separation of the treatment conditions in order to avoid contamination. Nevertheless, the study has to deal with difficulties specific to the psychopathology of anorexia nervosa. The treatment protocol allows for dealing with the typically occurring medical complications without dropping patients from the protocol. However, because patients are difficult to recruit and often ambivalent about treatment, a drop-out rate of 30% is assumed for sample size calculation. Due to the ethical problem of denying active treatment to patients with anorexia nervosa, the control group is defined as "treatment-as-usual".

**Trial registration:**

Current Controlled Trials ISRCTN72809357

## Background

Anorexia nervosa (AN) is a serious eating disorder marked by pronounced, self-induced underweight. Diagnostic criteria regarding weight are defined as maintenance of body weight < 85% of expected weight, or a body mass index (BMI) of < 17.5 kg/m^2 ^(DSM-IV; ICD-10). Weight reduction is induced by abnormal food restriction with or without purging behaviours such as self-induced vomiting, compulsive exercise, and/or use of laxatives and diuretics; other features include an intense fear of gaining weight and a distorted body image. The average prevalence rate of AN among young females is estimated to be 0.3% whereas the prevalence in men is about ten times lower [1]. Several long-term studies document the seriousness of anorexia nervosa [2], concluding that about half the patients fully recover from anorexia nervosa whereas a third improve and 20% remain chronically ill [3]. In a 21-year follow-up study of 84 patients, the crude mortality rate was 16% with a standardized mortality rate of 9.8 [4,5].

In regard to treatment efficacy, the evidence to date is judged to be weak [6]. In the guidelines of the British National Institute of Clinical Excellence [7], treatment recommendations for anorexia nervosa are based solely on expert reports and clinical experiences because clinical studies of good quality are absent. To date, only a few minor randomized controlled trials of individualized adult outpatient therapy for anorexia nervosa exist [8,9]. The trials are barely comparable as different types of psychotherapy and control groups were used. For instance, results of the study of Dare et al. [10] found no difference among the three specific therapies but showed that focal psychotherapy and family therapy were more effective in inducing weight gain than the control treatment (low-contact outpatient management). One trial found that a non-specific therapy was favoured over the two specific psychotherapies (cognitive behaviour therapy and interpersonal psychotherapy) [9]. However, no specific treatment was identified that was consistently superior to any other specific approach. Additionally, sample size in all studies was very small. Hay et al. [8], in their systematic review, therefore concluded that there is an urgent need for large multi-centre trials of commonly used psychotherapies for adults with anorexia nervosa.

In spite of an absence of evidence, many treatment approaches exist in clinical practice. In Germany, two commonly used treatment approaches are psychodynamic psychotherapy and cognitive behavioural therapy. In patients with anorexia nervosa, psychodynamic therapy addresses un- or pre-conscious conflicts that underlie the disorder. A basic approach of psychodynamic treatment in AN is to attend to the dysfunctional shaping of relationships and structural deficits in regard to the regulation of emotions that are relevant to the disordered eating behaviour [11]. Focal psychodynamic psychotherapy (FPT) was developed as a standardised form of time-limited psychodynamic psychotherapy [12].

In the treatment of eating disorders, the aims of cognitive behavioural therapy (CBT) focus on the modification of behaviours and cognitions that maintain the existing behaviour. Main foci are the modification of automatic negative thoughts and dysfunctional assumptions that relate to food, eating, weight, and body shape [13,14].

The aim of the ANTOP (Anorexia Nervosa Treatment of OutPatients) study is the examination of the efficacy of two standardised outpatient treatment programs for patients with anorexia nervosa – focal psychodynamic (FPT) and cognitive behavioural therapy (CBT) – in comparison to treatment-as-usual (TAU).

## Methods

### Study centres

This particular study is being carried out at 10 trial sites. Participating centres are the Departments of Psychosomatic Medicine and Psychotherapy of the Universities of Dortmund/Bochum, Erlangen, Essen, Freiburg, Hamburg, Heidelberg, München, Münster, Tübingen and Ulm. Patients are recruited in the outpatient departments of the hospitals. To increase the number of eligible patients, the study is advertised in local as well as regional media.

### Participants

Inclusion and exclusion criteria are listed in Table 1. According to these criteria, the sample of patients included in the study is representative of patients who qualify for treatment in an outpatient setting who suffer from either anorexia nervosa or subsyndromal anorexia nervosa.

**Table 1 T1:** Inclusion and exclusion criteria of the ANTOP study

Inclusion criteria	• AN and subsyndromal AN (lacking one diagnostic criterion according to DSM IV such as amenorrhea or weight phobia)
	• Female
	• Age 18 years or older
	• 15.0 < BMI < 18.5 kg/m^2^
	• written informed consent of the patient
Exclusion criteria	• Current substance abuse
	• Current medication with neuroleptics
	• Current suicidal ideation
	• Psychotic disorder
	• Bipolar disorder
	• Serious unstable medical problems/complications
	• Ongoing psychotherapy
	• Pregnancy
	• Clinically relevant cardiac arrhythmia
	• Primary somatic disease

### Interventions

Treatments for both the FPT and CBT groups are individual outpatient interventions, and are based on standardised treatment manuals. In these groups, the therapy is comprised of 40 sessions over a period of 10 months. This fixed time frame was chosen in accordance with the usual practice of the German health care system. CBT and FPT are time-limited treatment approaches that have a main advantage "to concentrate the mind of both the patient and the therapist" [13]. At the same time, patients with AN need a high intensity of treatment. Fairburn suggests a total of 40 CBT sessions for AN patients with a BMI between 15.0 and 17.5; this corresponds well to our study sample.

The frequency of the sessions is shown in Figure 1:

**Figure 1 F1:**

**Frequency of therapy sessions in the intervention conditions**. It has to be noted that a treatment period of 40 sessions does not equal always 10 months. We therefore defined the measurement point T2 as 10 months after inclusion in the study (± 2 weeks).

FPT and CBT sessions are audiotaped to monitor adherence to treatment manuals. Every ninth audiotape is checked by monitors in Tübingen (CBT) or Heidelberg (FPT) to ensure treatment integrity. To avoid contamination, the two treatments are provided by different therapists. Treatment providers – psychologists or medical doctors – are trained for a minimum of three years in the respective psychotherapy methods and receive additional training in the use of the manual. At every fourth session, experienced supervisors provide supervision to the therapists.

The psychodynamic treatment plan can roughly be subdivided into three treatment phases. The first phase focuses primarily on therapeutic alliance, ego-syntonicity of the disorder, and self-esteem. In the second phase of treatment, the main focus is placed on the association between interpersonal relationships and eating (anorectic) behaviour. In the last phase, relevant aspects are the transfer to everyday life, anticipation of treatment termination, and parting.

The cognitive behavioural treatment plan also consists of several treatment modules. The manual is based on the work of Fairburn [13]. Work sheets are adapted to Legenbauer & Vocks [15]. At each session, homework, work sheets, and exercises are assigned. The treatment plan focuses on patients' education about underweight and starvation as well as on the initiation and maintenance of regular dietary habits and weight gain. Enhancement of self-efficacy and self-monitoring are crucial elements of the entire treatment process. Further details of the two interventions are described in the treatment manuals [16].

The patients that are randomly assigned to the TAU control group receive support for further therapy planning. The patients receive a list of established outpatient therapists who practice psychotherapy in accordance with the general German psychotherapy guidelines. This is the standard approach for the allocation of patients to treatment in the German health care system with its sectoral separation of institutions that provide inpatient care and of individual practitioners that provide outpatient care. In the study protocol, the treatment (dosage and kind of therapy) in the TAU arm is not regulated in order to get a naturalistic and representative assessment of both the usual outpatient care and the psychotherapeutic treatment for patients with AN.

### Measurement time points

The time points of measurement are shown in Figure 2.

**Figure 2 F2:**
[figure not shown]
**Time points of measurement in the ANTOP study**.

A three-month follow-up is included in the first funding period of this study. Funding for a one-year follow-up has been applied for.

### Objectives and hypotheses

The objective of the current study is to assess whether two psychotherapeutic interventions are more effective than treatment-as-usual for the treatment of AN in adults. The primary hypothesis has two parts: Part one states that compared to treatment-as-usual, the specific psychotherapeutic outpatient intervention FPT shows a better outcome regarding the BMI at the end of treatment (T2). Part two states that compared to treatment-as-usual, the specific psychotherapeutic outpatient intervention CBT shows a better outcome regarding the BMI at the end of treatment (T2). That is, the null hypotheses tested in the confirmatory analysis are  and  where *μ *denotes the expected BMI value at the end of the respective treatment (T2), adjusted for the pre-randomization baseline BMI (T0).

Secondary (explorative) hypotheses state: (1) that the specific interventions (FPT, CBT) do not differ in terms of BMI increase at the end of treatment (T2); (2) that compared to TAU, FPT shows a better outcome at the end of treatment (T2) in regard to both a gain in quality of life and other psychosocial variables; (3) that compared to TAU, CBT shows a better outcome at the end of treatment in regard to both a gain in quality of life and other psychosocial variables.

### Outcomes

The primary outcome measure is the body mass index (BMI) at the end of the treatment (10 months after randomization). Secondary outcome measures are: the Morgan-Russell-criteria [17,18]; general axis I psychopathology (SCID I) [19]; eating disorder specific psychopathology (SIAB-Ex; Eating Disorder Inventory-2) [20,21]; severity of depressive comorbidity (PHQ-9) [22]; and quality of life according to the SF-36 [23]. The therapeutic alliance is assessed by the Helping Alliance Questionnaire (HAQ) [24]. Table 2 shows the assessments and outcome measurements at the different time points in the study.

**Table 2 T2:** Assessment of secondary outcome measures within the ANTOP study

	**Assessment**	
**Point in study**	**Expert rating**	**Self-report**

T0	SCID-I SIAB-Ex Morgan-Russell Outcome Assessment Schedule	EDI-2 PHQ-D SF-36
	
T1	Morgan-Russell Outcome Assessment Schedule	
	
T2	SCID-I SIAB-Ex Morgan-Russell Outcome Assessment Schedule	
	
T3	Morgan-Russell Outcome Assessment Schedule	

Monthly (during the treatment phase)		HAQ

EDI-2: Eating Disorder Inventory-2; HAQ: Helping Alliance Questionnaire; PHQ-D: German version of the Patient Health Questionnaire; SCID-I: Structured Clinical Interview for DSM-IV Axis I Disorders; SF-36: Questionnaire on health-related quality of life; SIAB-Ex: Structured expert interview for anorectic and bulimic eating disorders

Outcome assessments are either self-reported or performed by an independent blinded observer. Assessors are trained at the beginning of the study. Blinding of the participants is not possible.

### Sample size calculation

Estimates of a clinically relevant effect size were derived from two randomized controlled studies that evaluated the effects of FPT and CBT in outpatients with AN [10,25]. Based on these findings, it was assumed that the different interventions would result in an improvement of 1.0 BMI-points compared to the TAU-group, with a pooled standard deviation of 1.7 BMI-points (effect size = 0.59). As the hypothesis for the primary efficacy endpoint comprises two statistical tests, namely FPT vs. TAU and CBT vs. TAU, the nominal α-level was set to 2.5% (two-sided) in order to restrict the Type 1 error level to 5%. Calculations were done to detect an effect size of 0.59 for a comparison power of 80%. Using a two-sample t-test, a sample size of 55 patients per treatment arm was required, resulting in a total sample size of n = 3*55 = 165. Considering a non-compliance and loss to follow up rate of 30% in total, a minimum of 237 patients must be included in the study.

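### The equal 2.5% split over the two comparisons with TAU is valid, but Holm's step-down test would hold the same 5% with more power when both therapies work (optional, minor)

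*Protocol article*

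**What the plan says.** All of this is in the protocol article.

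- **Objectives and hypotheses:** "The primary hypothesis has two parts", one for FPT against TAU and one for CBT against TAU. Each has its own null hypothesis on BMI at the end of treatment.
- **Sample size calculation, multiplicity:** the primary hypothesis "comprises two statistical tests, namely FPT vs. TAU and CBT vs. TAU", so "the nominal α-level was set to 2.5% (two-sided) in order to restrict the Type 1 error level to 5"%.
- **Sample size calculation, planning values:** "an improvement of 1.0 BMI-points compared to the TAU-group, with a pooled standard deviation of 1.7 BMI-points (effect size = 0.59"). "Calculations were done to detect an effect size of 0.59 for a comparison power of 80"%.
- **Sample size calculation, result:** "Using a two-sample t-test, a sample size of 55 patients per treatment arm was required", "resulting in a total sample size of n = 3*55 = 165". After the allowance for loss: "Considering a non-compliance and loss to follow up rate of 30% in total, a minimum of 237 patients must be included in the study".
- **Statistical analysis:** both therapies are compared with the same TAU group in one mixed model, and the two treatment contrasts are named as confirmatory. This section gives no significance level, no order of testing and no rule for the second contrast once the first has been rejected.

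The 2.5% level in the sample-size section is therefore the only multiplicity rule in view.

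**The concern.** Read as it stands, the rule tests each contrast at 2.5% whatever happens to the other. Once one null hypothesis has been rejected, only one remains that could be falsely rejected, so the full 5% may be spent on it. Holm's procedure does this. It needs no further assumption, controls the family-wise error at 5% whichever of the two hypotheses are true, and can only add rejections to those of Bonferroni. Step-down Dunnett also uses the correlation that the shared TAU arm creates.

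At stake is power for the second comparison. The article plans for the same benefit from both therapies, which is the setting where a step-down rule gains most. It also describes patients as hard to recruit and assumes 30% loss, so power that costs no patients has some value.

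**Working it through.** **Inputs (protocol article).** Difference 1.0 BMI points, SD 1.7, two-sided 2.5% per comparison, 80% power, 30% loss, equal allocation to three arms. With equal arms and a shared control, the two test statistics have correlation 0.5.

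**1. The plan's own figure.** Normal approximation:

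n = 2(z₀.₉₈₇₅ + z₀.₈₀)² × SD² / difference² = 2 × (2.2414 + 0.8416)² × 1.7² / 1.0² = 54.94, so 55 per arm and 165 in total.

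With loss: 55 / 0.7 = 78.6, so 79 per arm, and 3 × 79 = 237. All three figures reproduce. The exact two-sample t-test has 79.0% power at 55 per arm, close enough to 80%.

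**2. Family-wise error of the split.** With correlation 0.5, the probability under the global null that at least one |Z| exceeds 2.2414 is 4.65%. So 5% is respected, with a little left unused. Dunnett's critical value that uses all of it is 2.212 (about 2.7% per test), or about 2.23 with 162 degrees of freedom.

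**3. Power of the three procedures.** Simulation with 2 million replicates: three arms of 55, variance pooled over the arms (162 degrees of freedom), critical values 2.262 at 2.5% and 1.975 at 5%.

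| True effects (BMI points) | Quantity | Bonferroni | Holm | Step-down Dunnett |
|---|---|---|---|---|
| 1.0 and 1.0 | power per comparison | 79.4% | 84.1% | 84.4% |
| 1.0 and 1.0 | power for both | 67.9% | 77.3% | 77.5% |
| 1.0 and 1.0 | power for at least one | 90.8% | 90.8% | 91.4% |
| 1.0 and 0.75 | power for the weaker | 52.2% | 61.1% | not computed |
| 1.0 and 0 | power for the effective one | 79.4% | 79.6% | 80.4% |
| 0 and 0 | family-wise error | 4.65% | 4.65% | 5.0% |

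Internal check: with equal effects, power per comparison is the mean of the at-least-one and both figures. Bonferroni: (90.8 + 67.9) / 2 = 79.4. Holm: (90.8 + 77.3) / 2 = 84.1.

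**4. Dependence on the number analysed.** The article plans intention to treat with LOCF, so all 79 per arm may enter the analysis. How far the effect would then be diluted is not given, so these cases are assumptions:

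- 79 per arm, 1.0 in both (undiluted): power for both 87.1% to 92.2% with Holm, about 5 points.
- 79 per arm, 0.75 in both: 55.4% to 66.1%, about 11 points.
- 79 per arm, 0.7 in both: again about 11 points.

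**The case against.** **Nothing is wrong with the split.** It aims to hold the type 1 error at 5%, and it does. A reader might infer from the word inefficient that the error rate or the sample size is faulty. Neither is: 55, 165 and 237 all reproduce, and the stated target of 80% per comparison is met to within about a point. This stands, and it limits the point to efficiency.

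**The rule for the second test is inferred.** A reader might conclude that the trial will certainly hold the second contrast at 2.5% after the first is rejected. The article does not say so. The level appears where the sample size is computed, and sizing each comparison at 2.5% is compatible with a Holm analysis, whose first step is at that level. The analysis plan is not shown and may name a step-down test. This also stands. The fixed split is the natural reading of the only rule in view, but the recommendation has to be conditional.

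**The gain depends on the scenario.** It would be wrong to say that power per comparison rises by 5 points in general. That needs both therapies to work as planned. Holm never changes the chance of at least one rejection. Power to show both therapies superior is also not a target that the article sets.

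**Bonferroni has a benefit.** One could claim that power is given up for nothing, but the equal split has simple simultaneous 97.5% intervals that always agree with its tests. A step-down rule loses that agreement. It also spends more of the permitted error: if one therapy works and the other does not, the chance of falsely rejecting for the ineffective one goes from 2.5% to about 4.2%, still below 5%.

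What survives is that, as a test, Holm rejects whenever Bonferroni does and sometimes more, at the same family-wise error and with no extra patients.

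**Conclusion.** The equal split is valid but less powerful than a step-down test. With 55 evaluable per arm and a 1.0-point effect of both therapies, Holm adds 84.1 − 79.4 = 4.7 points per comparison and 77.3 − 67.9 = 9.4 points for showing both. With effects of 1.0 and 0.75, it adds 61.1 − 52.2 = 8.9 points for the weaker therapy. If only one therapy works, it adds about 0.2 points, and step-down Dunnett about 1 point.

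These figures rest on the planning SD of 1.7, equal arms and a t-test. The mixed model with baseline BMI, and the number that LOCF keeps in the analysis, would shift the power levels.

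The gain should not be turned into a smaller trial. Holm would reach about 80% per comparison with 50 per arm, but only if both therapies work. Bonferroni gives 75% at that size, and at 55 per arm Holm adds almost nothing when one therapy is ineffective.

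Severity is minor: an optional improvement, conditional on the analysis plan not already providing it.

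**What to change.** Keep 55 evaluable per arm and 237 randomised. Before unblinding, unless the analysis plan already does so, add to the Statistical analysis section of the protocol: the two primary contrasts (FPT against TAU, CBT against TAU) are tested by Holm's procedure at a family-wise two-sided 5%; the smaller p-value is compared with 2.5% and, if that hypothesis is rejected, the other with 5%. Step-down Dunnett may be named instead; it needs the joint distribution of the two statistics and gains little beyond Holm. Name one of the two, not both.

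Continue to report 97.5% intervals for both contrasts.

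The cost is one sentence, with no change to randomisation, model or conduct. The drawback is that a 97.5% interval may include zero for a contrast that the step-down test rejects. The report should say in advance that the step-down test decides.

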### Randomization

Subjects are randomly assigned to the three groups. Randomization is stratified by duration of AN, resulting in two stratification groups. To ensure that allocation to the various groups is concealed, a centralized randomization is carried out by the Coordination Centre for Clinical Trials (KKS) in Marburg, Germany. Eligibility assessment, obtaining informed consent, and enrolling the patient in the trial is done by the respective study centres. The information data of the enrolled patient is transferred to the KKS by fax.

